## **3-2. Exclusion Criteria**

1) Patients who are pregnant or nursing, or who may become pregnant

2) Patients who have a history of hypersensitivity or have developed severe adverse events as a result of fluoropyrimidine drug use

3) Patients who have undergone organ transplantation

4) Patients with serious complicating conditions (interstitial pneumonia, pulmonary fibrosis, intestinal palsy, intestinal obstruction, poorly managed diabetes, cirrhosis, poorly managed hypertension, history of myocardial infarction within the prior 6 months, unstable angina, etc.)

5) Patients with multiple active* (*defined as cases with a disease-free period shorter than 5 years) cancers (excluding resolved skin basal cell carcinoma and cervical cancer, or gastric, esophageal, and M colon cancers confirmed to have been resolved as a result of endoscopic mucosal resection.)

*“Multiple cancer” is a blanket term encompassing both “multifocal” and “duplicative” cancers (Treatment Guidelines for Colorectal Cancer [7th edition])

6) Patients with uncontrollable advanced complicating infections

7) Patients otherwise deemed unsuitable for participation in this clinical trial by a physician

# **4. Subject Enrollment and Group Assignment**

## **4-1. Study Design**

Stage III (Dukes’ C)

Colorectal Cancer, Sigmoid Colon Cancer Cases

Curative Resection “Cur A”

Group Randomization

**Group A: Standard-of-Care**

Capecitabine 2 weeks on, 1 week off

8 courses (approx. 6 months)

**Group B: Study Treatment**

Capecitabine 2 weeks on, 1 week off

16 courses (approx. 12 months)

## **4-2. Subject Enrollment**

This study utilized centralized subject enrollment.

1) Register so that treatment can be started within 8 weeks after the date of surgery after confirmation of eligibility under “3. Selection Criteria”. (Note: enroll after confirmation of pathological test results)

2) After obtaining patient consent to study participation, fill out the "case registration form" (Form 1-1) and send to the secretariat via fax.

3) After receiving the case registration form via fax, the secretariat confirms that the prospective subject meets the selection criteria, then calls the study site supervisor as soon as possible. Subject group assignment then occurs, and dosing based on the subject total body surface area is communicated to the site by the secretariat, completing subject “enrollment”. The study secretariat then promptly sends the case registration confirmation form (Form 1-2) to the study site. Each site retains the case registration confirmation form on site and manages subject identification by creating a subject registry, etc.

4) The protocol treatment is initiated within 14 days after enrollment.

* “As soon as possible” means for subject enrollment (9:00-17:00) during business hours (Monday-Friday, excluding public holidays and the Year-End holiday period [December 29-January 4]), within “30 minutes” when submitted via paper during business hours (9:00-17:00) or between 9:00-9:30 the following business day if submitted outside of business hours (e.g., 9:00-9:30 on the next working day).

Japanese Foundation for Multidisciplinary Treatment of Cancer

[name]

[contact] (data center)

[name] (study representative/administration)

[name] (toll-free)

[contact]

E-mail: [contact] (data center)

Hours: Monday-Friday, 9:00-17:00 (excluding weekends, national holidays, and the New Year period (12/29–1/4))

## **4-3. Group Randomization**

The following factors are designated as adjustment factors to minimize bias during subject randomization.

1) N-factor (N1/N2, N3)

2) Study site

**5. Treatment Procedures**

## **5-1. Protocol Treatment**

The protocol treatment assigned to each subject starts within 8 weeks after surgery. Subjects’ height and body weight at enrollment are used to calculate dosage, and no dose correction due to changes in body weight is performed.

## **5-2. Study Drug**

Capecitabine

- Xeloda® tablets 300 (Chugai Pharmaceutical Co., Ltd.)

1 tablet contains 300 mg of capecitabine

## **5-3. Dosing Schedule**

**5-3-1. Group A: Standard-of-care group (8 courses [approx. 6 months])**

Capecitabine (Xeloda tablets): Patients will receive the established dosage of capecitabine (1,250 mg/m2) based on their total body surface area (1,500 mg–2,400 mg) twice daily (after breakfast and within 30 minutes after dinner) for 14 days continuously followed by a 7-day off period. This 3-week period will comprise 1 course of treatment. Patients will receive 8 courses in total.

After completing all 8 courses, patients not exhibiting cancerous recurrence will undergo continuous monitoring without additional treatment.

**5-3-2. Group B: Study treatment group (16 courses [approx. 12 months])**

Capecitabine (Xeloda tablets): Patients will receive the established dosage of capecitabine (1,250 mg/m2) based on their total body surface area (1,500 mg–2,400 mg) twice daily (after breakfast and within 30 minutes after dinner) for 14 days continuously followed by a 7-day off period. This 3-week period will comprise 1 course of treatment. Patients will receive 16 courses in total.

After completing all 16 courses, patients not exhibiting cancerous recurrence will undergo continuous monitoring without additional treatment.

**5-3-3. Established capecitabine dosages**

The actual dosages of capecitabine administered are as follows.

No dose corrections due to changes in body weight are performed after protocol treatment initiation.

Table 2 Per-administration capecitabine dosages by subject total body surface area (Groups A and B)

| Body Surface Area | Single-dose Volume |
| --- | --- |
| ≤1.33 m2 | 1,500 mg (5 tablets) |
| ≥1.33 m2 ≤1.57 m2 | 1,800 mg (6 tablets) |
| ≥1.57 m2 ≤1.81 m2 | 2,100 mg (7 tablets) |
| ≥1.81 m2 | 2,400 mg (8 tablets) |

**5-4-2. Off-drug periods/dose reductions/therapy reinitiation provisions**

Adverse events are evaluated based on the Japanese-language Common Terminology Criteria for Adverse Events (CTCAE) v3.0 Japan Clinical Oncology Group/Japan Society of Clinical Oncology (JCOG/JSCO) version. Off-drug periods, dose reduction, and therapy reinitiation due to the occurrence of adverse events during capecitabine administration are managed according to “Table 3 Off-period/dose reduction criteria” and “Table 4 Reduced dosages”. In addition, handling of Grade II/III hand-foot syndrome, diarrhea, nausea, and vomiting shall be performed in accordance with “5-4-3. Provisions for off-drug periods/dose reductions/therapy reinitiation following adverse events not falling under the above”.

Clinical laboratory values may also be treated as adverse events in the following cases only:

(1) In case of a serious adverse event

(2) In cases where dose reduction, an off-period, or discontinuation of the protocol treatment is necessary

(3) When medical treatment is necessary

(4) When determined to be clinically problematic

1) Warnings concerning off-drug periods, dose reductions, and therapy reinitiation provision are as follows.

(1) Off-drug periods and dose reduction owing to worsening complications observed before the start of administration may be arranged based on fluctuations in adverse event grade, if deemed appropriate by the attending physician. For example, if Grade I alkaline phosphatase before administration deteriorates to Grade II during capecitabine administration, this may be treated as a Grade I adverse event, understood as a shift in adverse event grade.

(2) If the attending physician determines that adverse events do not cause interruption or delays in administration, such as in cases of alopecia or dysgeusia, and it is determined that there is no possibility of the event becoming serious, administration of capecitabine may be continued at the same dosage without an off-period or dose reduction.

(3) When anemia is controllable by transfusion, there is no need for an off-period or dose reduction, and treatment may continue at the same dose.

(4) If adverse events of Grade II appear at the end of 2 weeks of capecitabine administration and recover to Grade 0–I during the 1 week off-period prescribed by the treatment protocol, “Table 3 Off-period/dose reduction criteria” does not apply, and treatment may continue without changes as deemed appropriate by the attending physician.

(5) An off-drug period should be considered during the 2 weeks of administration as a non-administration day and the administration schedule should be maintained (2 weeks on, 1 week off). Capecitabine not administered because of an off-drug period should not be re-administered. If the start of an individual treatment course is delayed, the 3-week following the start date shall constitute 1 course.

(6) If a dose reduction is performed, the dose should not be increased later.

(7) If treatment initiation is delayed for more than 3 weeks or an adverse event requiring discontinuation appears, the protocol treatment is deemed to have been discontinued.

(8) Although patient withdrawal based on self-determination is acceptable, such patients should be instructed to contact their attending physician or his/her proxy to the extent possible. The patient’s drug adherence should also be checked upon visitation.

2) The following are provisions for drug off-periods due to the occurrence of adverse events during treatment.

(1) When an adverse event of Grade I has appeared

Administration may be continued without changes.

(2) When an adverse event of Grade II or higher appears

Off-drug periods, dose reductions, and therapy reinitiation should be conducted according to “Table 3 Off-period/dose reduction criteria” below. For individual subjects, confirm the dose reduction based on the “registration confirmation form”. A single dose at the time of dose reduction and the number of single dose tablets are calculated based on “Table 4 Reduced dosages”. A single dose at the time of dose reduction is determined according to the subject’s total body surface area at the time of enrollment.

Table 3 Off-period/dose reduction criteria

|  |  | Countermeasures during treatment period | Treatment reinitiation dosages |
| --- | --- | --- | --- |
| Grade 1 |  | Off-period/dose reduction not needed | Dose reduction not needed |
| Grade 2 | 1st onset  2nd onset  3rd onset  4th onset | Off-drug until improvement to Grade 0-1  Off-drug until improvement to Grade 0-1  Off-drug until improvement to Grade 0-1  Suspend protocol treatment | Dose reduction not needed  Dose reduction 1  Dose reduction 2  － |
| Grade 3 | 1st onset  2nd onset  3rd onset | Off-drug until improvement to Grade 0-1  Off-drug until improvement to Grade 0-1  Suspend protocol treatment | Dose reduction 1  Dose reduction 2  － |
| Grade 4 |  | Suspend protocol treatment | － |

Note) Number of onsets refers to the number of appearances of events of the same grade, and is not limited to the number of appearances of the same event.

Table 4 Reduced dosages

| Body surface area | Single dose | | |
| --- | --- | --- | --- |
| Initial dose | Dose reduction 1 | Dose reduction 2 |
| ≤1.13 m2 | 1,500 mg (5 tablets) | 900 mg (3 tablets) | 600 mg (2 tablets) |
| ≥1.13 m2　≤1.21 m2 | 1,200 mg (4 tablets) |
| ≥1.21 m2　≤1.33 m2 | 900 mg (3 tablets) |
| ≥1.33 m2　≤1.45 m2 | 1,800 mg (6 tablets) |
| ≥1.45 m2　≤1.57 m2 | 1,500 mg (5 tablets) |
| ≥1.57 m2　≤1.69 m2 | 2,100 mg (7 tablets) |
| ≥1.69 m2　≤1.77 m2 | 1,200 mg (4 tablets) |
| ≥1.77 m2　≤1.81 m2 | 1,800 mg (6 tablets) |
| ≥1.81 m2 | 2,400 mg (8 tablets) |

**5-4-3. Provisions for off-drug periods/dose reductions/therapy reinitiation following adverse events not falling under the above**

1) Grade II/III hand and foot syndrome

Adverse event grade is determined based on the criteria in “Table 5 Diagnostic criteria for hand-foot syndrome” below and subject to “Table 3 Off-period/dose reduction criteria” above.

Table 5 Diagnostic criteria for hand-foot syndrome

| Grade | Clinical area | Functional area |
| --- | --- | --- |
| 1 | Numbness, skin hypersensitivity, burning, tingling, painless swelling, painless erythema | Everyday activities are not impaired |
| 2 | Swelling accompanying painful skin erythema | Everyday activities are somewhat impaired |
| 3 | Moist desquamation, ulcers, blisters, strong pain | Everyday activities are impossible |

If the grade of the corresponding symptom is inconsistent between the diagnostic areas (clinical area, functional area), adopt a grade that can be determined to be more suitable.

This criterion applies only to the diagnosis of hand-foot syndrome, and not to diagnoses of skin or other organ-related symptoms.

2) Grade II/III diarrhea, nausea, and emesis

Discontinue capecitabine use and take appropriate countermeasures.

If symptoms can be controlled with treatment intervention within 2 days, the protocol treatment may be resumed without changes. If control requires more than 3 days, “Table 3 Off-period/dose reduction criteria” should be followed (including diarrhea determined to require more than 3 days for diagnosis or treatment due to the possibility of dihydropyrimidine dehydrogenase [DPD] deficiency, etc.)

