## **5-5. Treatment Discontinuation Provisions**

**5-5-1. Treatment discontinuation criteria**

If applicable, the attending physician will discontinue subsequent treatments and take appropriate measures. Investigators should observe and inspect for the evaluation items specified in “Table 6 Examination items and evaluation schedule” below at the time of discontinuation and record their findings and the accompanying rationale in their case report. In cases of termination, the attending physician shall promptly submit an administration progress survey to the study secretariat via fax.

1) When a subject him/herself withdraws consent

2) When a subject him/herself requests discontinuation of the protocol treatment

3) When recurrence of the original disease is observed

4) When novel cancerous lesions (duplicated cancer or multifocal colorectal cancer [excluding M cancer]) occurs

5) When the attending physician determines that protocol continuation will be difficult due to deterioration of comorbidities or onset of complications

6) When there is no relief or disappearance of symptoms following withdrawal due to an adverse event that falls under the off-period/dose reduction provisions (delay of treatment start by over 3 weeks or withdrawal)

7) If administration cannot be continued due to the occurrence of an adverse event even after 1 or 2 level reductions under the off-period/dose reduction provisions

8) If an adverse event of Grade IV occurs, the protocol treatment must be discontinued. (If capecitabine treatment is restarted at the discretion of the attending physician after protocol termination, a case report must be submitted.)

9) When the attending physician determines that protocol continuation will be difficult owing to an adverse event

10) If a subject dies

11) When the protocol treatment cannot be continued because the subject was transferred to a hospital

12) If a subject is determined to be ineligible after enrollment

13) Other cases in which the attending physician deems it necessary to terminate the protocol treatment

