# **13. Amendments to the Clinical Study Protocol**

If it is necessary to amend this study protocol or patient briefing materials during assessment, the study representative will revise such materials with the approval of the Clinical Trial Review Committee. The amended study protocol or patient briefing materials shall be approved by the Ethics Committee (or IRB) of each study site.

This does not apply to protocols that do not carry the possibility of increasing the risk borne by patients participating in the study and that are not related to the primary endpoint of the study.

If it is necessary to amend this study protocol, participant enrollment shall be temporarily suspended and resumed after revisions are completed. However, this policy does not apply if the proposed amendment does not directly affect subject enrollment.

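### Table 3 counts Grade 2 and Grade 3 onsets separately, so after two Grade 2 onsets a first Grade 3 event restarts at the dose in use, while a third Grade 2 event would lower it

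*Protocol*

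**What the plan says.** Section 5-4-2 of the Protocol makes Table 3 the governing rule for events of Grade 2 or higher.

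- **Grade 2 row:** the first onset restarts without reduction, the second at Dose reduction 1, the third at Dose reduction 2, and the fourth suspends protocol treatment.
- **Grade 3 row:** the first onset restarts at Dose reduction 1, the second at Dose reduction 2, and the third suspends.
- **Counting (Note to Table 3):** "Number of onsets refers to the number of appearances of events of the same grade". Different event types share one count, but each grade has its own.
- **Dose levels:** Table 4 gives the two reductions as fixed doses by body surface area. They are not steps relative to the current dose.
- **Rule 1)(6):** "If a dose reduction is performed, the dose should not be increased later".
- **Recovery:** each restart in Table 3 carries the condition "Off-drug until improvement to Grade 0-1". Rule 1)(7) ends protocol treatment in this case: "If treatment initiation is delayed for more than 3 weeks or an adverse event requiring discontinuation appears".
- **Stopping:** section 5-5-1 item 7 has the physician discontinue in this case: "If administration cannot be continued due to the occurrence of an adverse event even after 1 or 2 level reductions". Items 9 and 13 add general physician judgement.

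**The concern.** Both rows of Table 3 treat Grade 3 as the worse event: the dose falls at the first onset instead of the second, and treatment ends at the third instead of the fourth. Because the counts are separate and the levels fixed, earlier Grade 2 onsets can lower the dose without moving the patient along the Grade 3 row. A first Grade 3 event may then call for a level the patient has already reached.

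What is at stake is patient safety. After a Grade 3 toxicity the patient would resume the dose that produced it, although a milder event at the same point would have brought a lower dose. At least three counted onsets are needed, so 16 courses (Group B) leave more room for this than 8 (Group A).

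**Working it through.** **Inputs.** The two rows of Table 3, the Note, and rule 1)(6), all in section 5-4-2. The plan states no figure of its own to reproduce.

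**Method.** Write the state as (prior Grade 2 onsets, prior Grade 3 onsets). Before suspension the first runs from 0 to 3 and the second from 0 to 2, giving 4 × 3 = 12 states. By rule 1)(6), the dose in use is the lower of the levels that the two rows have so far called for. The dose after the next event is the lower of the dose in use and the level named in that event's row. DR1 and DR2 stand for Dose reduction 1 and 2.

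| State | Dose in use | Next Grade 2 | Next Grade 3 | Grade 3 compared with Grade 2 |
|---|---|---|---|---|
| (0,0) | initial | initial | DR1 | stricter |
| (0,1) | DR1 | DR1 | DR2 | stricter |
| (0,2) | DR2 | DR2 | suspend | stricter |
| (1,0) | initial | DR1 | DR1 | equal |
| (1,1) | DR1 | DR1 | DR2 | stricter |
| (1,2) | DR2 | DR2 | suspend | stricter |
| (2,0) | DR1 | DR2 | DR1 | **more lenient** |
| (2,1) | DR1 | DR2 | DR2 | equal |
| (2,2) | DR2 | DR2 | suspend | stricter |
| (3,0) | DR2 | suspend | DR2 | **more lenient** |
| (3,1) | DR2 | suspend | DR2 | **more lenient** |
| (3,2) | DR2 | suspend | suspend | equal |

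**Result.** Six states are stricter for Grade 3, three are equal and three are reversed. A Grade 3 event leads to a restart in 8 states (none or one prior Grade 3 onset: 4 × 2). In exactly the three reversed states that restart is at the dose in use; in the other five it brings a reduction. At (3,0) the Grade 3 row taken alone names DR1 for a patient already at DR2, and only rule 1)(6) prevents an increase. The same three states are reversed whether or not rule 1)(6) is applied.

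**Do other provisions close the gap?**

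- The recovery condition, the 3-week limit and the suitability check in section 5-4-1 govern whether and when treatment resumes. They do not set the dose.
- Section 5-5-1 items 7, 9 and 13 concern stopping. None sets the restart dose at (2,0).
- At (3,0) and (3,1) two reductions have already been made, so item 7 bears directly on the decision.

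**Size at (2,0).** In the 1.13 m² or less band of Table 4, DR1 is 900 mg and DR2 is 600 mg. The reduction not made is 900 − 600 = 300 mg per administration, or 300/900 = 33% of the dose in use. This is the only row of Table 4 that can be read complete in the extracted text.

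**Check of the fix.** Suppose a Grade 3 event at a reduced dose goes one level lower and at DR2 suspends treatment. Then (2,0) gives DR2, equal to the next Grade 2 event, and (3,0) and (3,1) give suspension, also equal. Reversed states fall from 3 to 0. The sequences 2-2-2-2 and 3-3-3 keep their present outcomes, as does 2-3.

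**The case against.** The strongest case against runs as follows.

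- **Item 7 may already cover two of the three states.** At (3,0) and (3,1) the patient is at the lowest level and the Grade 3 event has interrupted dosing. In each single-grade sequence the next counted event at that level ends treatment, which suggests what was intended. This stands in part. A reader might infer that the protocol leaves these patients on treatment with no route to a stop, and the documents do not support that. Equally, item 7 does not clearly require a stop once the event has recovered in time and the physician judges that dosing can go on. Nor does item 7 cure (2,0): it cannot sensibly apply to every interruption after one reduction.

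- **Restarting at an unchanged dose is not foreign to this protocol.** For Grade 2 or 3 diarrhea, nausea and emesis, section 5-4-3 item 2 says: "If symptoms can be controlled with treatment intervention within 2 days, the protocol treatment may be resumed without changes". At (2,0) the Grade 3 event is the patient's first and may be a different toxicity from the earlier ones. Separate counting can be a legitimate clinical choice. What remains is the inconsistency: with pooled event types, a third Grade 2 event of any kind lowers the dose at that point and a Grade 3 event does not. No reason is given.

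- **Three of 12 is a count of table states, not a frequency.** This stands. The reversals occur at the third, fourth and fifth counted onset respectively. Rules 1)(2) to 1)(4) and section 5-4-3 item 2 take some events out of Table 3, and the protocol gives no onset rates.

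**Conclusion.** The point holds firmly at (2,0): a first Grade 3 event after two Grade 2 onsets restarts at Dose reduction 1, already in use, where a third Grade 2 event would lead to Dose reduction 2, and no other text sets a lower dose. At (3,0) and (3,1) the literal table is reversed as well, but the practical gap depends on how section 5-5-1 item 7 is read.

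The documented size is 900 versus 600 mg per administration in the lowest body surface area band. Differences in the other bands would require filling cells that are blank in the extracted Table 4, so none is claimed. The number of patients affected is unknown.

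A reader might infer that the reversal biases the comparison of 8 with 16 courses or weakens the trial statistically. The documents do not support that: the sample size, alpha and primary DFS analysis do not depend on this rule. It is a minor safety correction to a dosing instruction, and worth making because it is short and follows Table 3's own ordering of the grades.

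**What to change.** Add one sentence to the Note under Table 3: a Grade 3 event at an already reduced dose restarts one level below the current dose, and protocol treatment is suspended if a Grade 3 event occurs at Dose reduction 2. A cross-reference to rule 1)(6) would help.

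**Effect on dosing.** Some patients would receive a lower dose or stop earlier. The number is probably small but cannot be quantified, and there is more room for it in Group B. Ten four-onset orderings now end in a restart: four with three Grade 2 and one Grade 3 onset, and six with two of each. Two of the ten, 2-2-2-3 and 2-2-3-3, would become suspensions.

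**Limits.** The outcome comes to depend on order: 2-2-3-3 is suspended, while 2-3-2-3 and 3-2-2-3 restart at Dose reduction 2. Five of the 10 orderings of three Grade 2 and two Grade 3 onsets still reach no suspension; at present none of the 10 does.

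**Administrative cost.** This is an amendment under section 13, which needs review-committee approval and adds: "The amended study protocol or patient briefing materials shall be approved by the Ethics Committee (or IRB) of each study site". The exception for changes that cannot raise patient risk and are unrelated to the primary endpoint is not clearly available, because a dosing rule affects exposure in the DFS comparison. Section 13 also pauses enrollment for an amendment unless the change has no direct effect on enrollment; a dosing clarification arguably has none, but that should be settled beforehand. No extra patients, visits or data are needed.
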